### 5.3 Subject Exclusion Criteria

Subjects meeting any of the exclusion criteria at baseline will be excluded from the study.

- Consumption of supplements or food products containing LGG or probiotics for 28 days prior to the start of the study or consumption of yogurt that has the “live and active cultures” seal.
- Known or suspected allergies to probiotics, *Lactobacillus*, microcrystalline cellulose, gelatin, or antibiotics that may be used to treat LGG bacteremia or infection (i.e. subject able to tolerate at least 2 of the following regimens - Ampicillin or other beta lactam antibiotic, and Clindamycin, and Moxifloxacin).
- Received oral or parenteral antibiotics within 4 weeks of enrollment or prescribed antibiotics on the day of enrollment
- Drug or alcohol abuse within the previous 12 months
- Hospitalization, major surgery or endoscopy within the last 3 months
- Scheduled hospital admission within 3 months of enrollment
- Resident of a nursing home or rehabilitation center
- Presence of any of the following:
  - Grade 2 or higher abnormal vital signs or abnormalities on physical exam (Appendix A)
  - Indwelling catheter or implanted hardware/prosthetic device or feeding tube
  - Current or within the last 2 years, any episode of bowel leak, acute abdomen, diverticulitis, colitis, bloody bowel movements or peptic ulcer disease, including any surgical procedure or current prescription medications for any of these conditions
  - Current or within the last four weeks, active bowel disease such as an episode of infectious or non-infectious diarrhea, constipation, or vomiting lasting more than 12 hours or current prescription medications for any of these conditions

- Any history of gastric or intestinal dysmobility, slowed transit time, variable small intestinal permeability, pancreatitis, history of gastrointestinal tract cancer or metastasis, or inflammatory bowel disease or current prescription medications for any of these conditions
- Any history of Hepatitis B or Hepatitis C infections, cirrhosis, or chronic liver disease
- Underlying structural heart disease such as abnormal native heart valve or congenital abnormality, previous history of endocarditis or valve replacement, Stage IV congestive heart failure
- History of peripheral vascular disease or stroke

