## 9.6 Rescue Medication

There is a theoretical risk of translocation of LGG across the bowel wall and resultant clinical infection caused by *Lactobacillus*. Possible infections include bacteremia, endocarditis, or abscesses. The antibiotic susceptibilities of LGG, as reported by various researchers, are attached (Appendix C). Based on the available literature, including experimental models of infective endocarditis with *Lactobacillus plantarum*, we would recommend treatment of *Lactobacillus* endocarditis with a beta-lactam and gentamicin, but bacteremia alone or other sites of infection may be treatable with a beta lactam only. If any study subject develops invasive disease

(bacteremia, endocarditis, etc.), we will recommend this treatment course, but will also ask that an independent infectious disease physician (not involved in the study) evaluate and treat the subject. We will also obtain *in vitro* sensitivity data on the specific isolate as several articles show a benefit of treating with antibiotics to which the organism is sensitive *in vitro*.

The dose, route, frequency, and duration of treatment will be determined by the infectious disease consultant caring for the subject but the recommended regimens are as follows:

Ampicillin 2 grams intravenously every 6 hours (or alternative beta-lactam antibiotic) for 14 days  
or  
Clindamycin 900 mg intravenously every 8 hours for 14 days or  
Moxifloxacin 400 mg intravenously every 24 hours for 14 days

Alternative oral regimens for these 3 drugs should the subject be able to transition to an oral regimen to complete the 14 days of therapy are as follows:

Ampicillin 500 mg orally every 6 hours (or alternative beta-lactam antibiotic) for 14 days or  
Clindamycin 300 mg orally every 8 hours for 14 days or  
Moxifloxacin 400 mg orally once a day for 14 days

At the conclusion of therapy for invasive disease, we will obtain throat and stool cultures to determine whether the subject is colonized with LGG in either of these locations. The *in vitro* susceptibility pattern of the isolate will be rechecked to guide additional antibiotic therapy to eradicate the LGG. Subjects will be followed until LGG is no longer isolated from these potential colonizing sites.

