## APPENDIX B: ANTIBIOTIC SUSCEPTIBILITIES

Valio Ltd. Research and Development, June 2004.

Table 1. Antibiotic susceptibility of *Lactobacillus* GG

| Antibiotics                      | Minimum inhibitory concentration (MIC) µg/ml                   |                           |                                                               |                                                                                           |                                                                          |
|----------------------------------|----------------------------------------------------------------|---------------------------|---------------------------------------------------------------|-------------------------------------------------------------------------------------------|--------------------------------------------------------------------------|
|                                  | Yhtyneet
Laboratoriot Ltd,
Finland Σ-teet, AB
Biodisc | Vanderhoof et al,
1999 | Klein et al, 2000
MD Plate Gram
Positive,
Radiometer | NCCLS Agar
Dilution using
Brucella agar + 5%
SRBC
[name]
Feb 4, 2004 | Brain Heart
Infusion Broth
Dilution
[name]
Jan 4, 1996 |
| (Benzyl)penicillin               | 0.19                                                           | 1.0                       | 0.25                                                          |                                                                                           | 0.25                                                                     |
| Ciprofloxacin                    | 2.0                                                            | 0.2                       | >4                                                            |                                                                                           | 1                                                                        |
| Ofloxacin                        |                                                                |                           |                                                               |                                                                                           | 2                                                                        |

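### Section 9.6 gives two different recommendations for invasive Lactobacillus infection, and the 5.3 antibiotic-tolerance criterion, itself inconsistent, matches only one of them

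*Protocol*

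**What the plan says.** **Entry (Protocol 5.3).** One exclusion bullet covers known or suspected allergy to several items, ending with "or antibiotics that may be used to treat LGG bacteremia or infection". A parenthesis opening with i.e. follows and describes a "subject able to tolerate at least 2 of the following regimens - Ampicillin or other beta lactam antibiotic, and Clindamycin, and Moxifloxacin". Gentamicin is not mentioned.

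**Rescue, narrative (Protocol 9.6).** After naming bacteremia, endocarditis and abscesses as possible infections, the section recommends treating "endocarditis with a beta-lactam and gentamicin, but bacteremia alone or other sites of infection may be treatable with a beta lactam only". It then applies this to any subject with invasive disease: "bacteremia, endocarditis, etc.), we will recommend this treatment course, but will also ask that an independent infectious disease physician" evaluate and treat the subject.

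**Rescue, list (Protocol 9.6).** The next paragraph leaves dose, route, frequency and duration to the consultant, "but the recommended regimens are as follows". The first intravenous item is "Ampicillin 2 grams intravenously every 6 hours (or alternative beta-lactam antibiotic) for 14 days". Clindamycin and moxifloxacin follow, joined by the word or. The oral list has the same three options.

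**Susceptibilities.** Section 9.6 states that the antibiotic susceptibilities of LGG, "as reported by various researchers, are attached (Appendix C"). The table is under "APPENDIX B: ANTIBIOTIC SUSCEPTIBILITIES". Appendix C is the symptom diary, and section 7.2 (telephone calls) cites it correctly as such.

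**The concern.** The tolerance criterion has one purpose: to make sure that a subject who develops an LGG infection can take the treatment the protocol plans. For that, the plan has to be single and the criterion has to refer to it. Neither holds.

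A physician reading 9.6 for a subject with endocarditis finds a two-drug combination in one paragraph and, in the next, a list of alternatives without the second drug. A screener reading 5.3 for a subject who can take no beta-lactam finds an opening clause that excludes the subject and an explanation that admits the same subject. Two institutions screen for this trial (section 5), so the wording should not leave the decision to whoever reads it. The wrong appendix reference would be met at the moment when someone needs the susceptibility table quickly.

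The trial's primary objective is safety, and 9.6 exists because translocation with clinical infection is a recognised, though theoretical, risk. Table 4 includes two published cases aged 74 and 67, within the trial's 65-80 range.

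**Working it through.** The plan gives no figure on this point. The check compares the passages and counts the tolerance patterns that the rule admits.

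**1. The two recommendations in 9.6**

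| Situation | Narrative | Regimen list |
|---|---|---|
| Endocarditis | Beta-lactam plus gentamicin | No separate entry; gentamicin absent |
| Bacteremia or other sites | Beta-lactam only may suffice | Beta-lactam, or clindamycin, or moxifloxacin |
| Scope stated | Any invasive disease | No restriction by type of infection |

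The two differ in both rows.

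**2. Which one 5.3 matches**

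The three options in 5.3 are the three in the regimen list. Compared with the narrative, 5.3 lacks gentamicin and adds two drugs that the narrative does not name.

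**3. Patterns admitted by the two-of-three wording**

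Write each pattern as (beta-lactam, clindamycin, moxifloxacin), with 1 for tolerated and 0 for not. Any tolerated beta-lactam counts as 1, as the criterion allows. There are 2^3 = 8 patterns. The rule needs a sum of at least 2:

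- (1,1,1), (1,1,0), (1,0,1) and (0,1,1) pass, which is 4 of 8.
- (0,1,1) has no beta-lactam, which is 1 of the 4.

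Add gentamicin as a fourth drug that is not screened: 2^4 = 16 patterns, of which 4 x 2 = 8 pass. Those that can take a beta-lactam and gentamicin number 3 x 1 = 3, so 8 - 3 = 5 of the 8 cannot take the narrative's endocarditis combination.

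**4. The opening clause of 5.3 read alone**

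Treat an untolerated drug as an allergy, and count only the three listed options as possible treatments. The opening clause then admits only (1,1,1). The explanation admits four patterns. The two parts of the bullet disagree on 4 - 1 = 3 of the 8.

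These are counts of patterns, not probabilities.

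**5. How often it could arise (assumption)**

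The protocol gives no frequency of beta-lactam intolerance. Let q be the assumed proportion among enrolled subjects, each otherwise eligible. The chance of at least one such subject among n is 1 - (1 - q)^n.

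| q (assumed) | n = 10 | n = 15 |
|---|---|---|
| 2% | 18% | 26% |
| 5% | 40% | 54% |
| 10% | 65% | 79% |
| 15% | 80% | 91% |

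For example, 1 - 0.95^10 = 0.401. This is the chance that the eligibility question arises at all. It is not the chance that a subject needs rescue and cannot receive it.

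**The case against.** The strongest reply is that 5.3 fits what 9.6 itself calls its recommended regimens, drug for drug, so every admitted subject tolerates at least two of them. The independent physician evaluates and treats, the subject's own isolate is tested, and the narrative's wording for bacteremia is permissive. Section 5.3 also excludes structural heart disease, previous endocarditis, valve replacement, implanted hardware and immunosuppression, and section 2.1.6.2 rates the risk of invasive disease as low. All of this stands. It limits the consequence, but it does not remove the difference between the two parts of 9.6.

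A second reply is that the list might be meant only for infections other than endocarditis. Its lead-in does not say so, and for bacteremia it still adds two drugs that the narrative does not name.

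A third is that i.e. introduces a definition, so the two-of-three test governs. That is the natural reading, and the bullet should then be worded that way.

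A reader might also infer that 9.6 conflicts with the minimum inhibitory concentrations (MICs) in Appendix B: gentamicin is listed at 24 and >32 µg/ml, and some agents that would count as another beta-lactam at >128 or >256. The documents do not support that inference. Appendix B gives no breakpoints, and its columns come from different laboratories and methods. Gentamicin is named only in combination, and 9.6 cites an experimental endocarditis study (reference 226) whose title reports synergy of penicillin with gentamicin. A subject whose only tolerated beta-lactam is a high-MIC agent must still tolerate clindamycin (0.25-1) or moxifloxacin (1) to qualify, and these values are close to ampicillin's 0.5-1.

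**Conclusion.** The point holds as a textual inconsistency in the eligibility and rescue sections, and it should be fixed. Three defects are on the page and need no assumption:

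- The narrative and the regimen list in 9.6 disagree on gentamicin and on the non-beta-lactam alternatives.
- The opening clause of the 5.3 criterion and its explanation disagree, and the explanation is aligned only with the list. One of four admitted patterns has no beta-lactam, and gentamicin tolerance is not screened in any.
- The susceptibility reference points to the wrong appendix.

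It does not follow that subjects would be enrolled without a rescue option, that 5.3 misses the rescue plan as a whole, or that the sites would in fact decide differently. The first two are contradicted by the match with the regimen list, and the third is only a possibility that the wording leaves open. The frequency table rests entirely on assumed prevalences. The sample size of 10-15, the outcome measures and the analysis are unaffected.

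**What to change.** 1. In 9.6, reconcile the narrative with the regimen list so that the section makes one recommendation for each type of infection it covers.
2. In 5.3, align the opening clause and the two-of-three explanation with each other and with the reconciled 9.6, so that the bullet gives one answer for any subject. If gentamicin remains in 9.6, state whether tolerance of it is part of the criterion.
3. In 9.6, change the susceptibility reference from Appendix C to Appendix B.

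Which agents are recommended and which entry rule applies are for the investigators and their infectious disease consultant to decide; this review proposes neither.

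The cost is a short amendment to 5.3 and 9.6 and a matching change to any screening form. Any effect on screen failures among the 80 planned screenings depends on the entry rule chosen. No statistical section needs revision.

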## **5.4 Enrollment**

Subjects who meet all inclusion and have no exclusion criteria and who return for their baseline appointment are enrolled into the study. On enrollment, they will receive a unique study ID that will be used on all study forms and labels. Willingness to proceed is reviewed at each visit. In addition, subjects who enroll in this study will be informed of an optional sub study.

## 6 STUDY DRUG

### 6.1 Study Product Description

#### 6.1.1 Acquisition

The study drug (LGG) will be supplied in blister packs by Amerifit Brands, Inc. Amerifit Brands, Inc. will ship the study drug via UPS overnight with ice packs to the research pharmacy at Tufts Medical Center and Massachusetts General Hospital. Upon receipt, the research pharmacist at Tufts Medical Center and Massachusetts General Hospital will inventory the contents of the shipment received, confirm the contents match with the shipping paperwork, and document the receipt of the shipment in log books to be maintained by the research pharmacy.

#### 6.1.2 Formulation, Packaging, and Labeling

*Lactobacillus rhamnosus* GG, ATCC 53103 (LGG) is supplied in a gelatin capsule at a dosage of  $1 \times 10^{10}$  LGG per capsule. The capsule also contains microcrystalline cellulose (purified partially depolymerized cellulose), an inactive ingredient. Each capsule is wrapped in double foil to protect it against harmful light, air, and moisture and provided in blister packs. The blister packs are labeled with the lot number of the study drug prior to shipping to Tufts Medical Center and Massachusetts General Hospital.

#### 6.1.3 Product Storage and Stability

The LGG capsules should be stored in a cool, dry place at or below 72-75°F. Although LGG capsules do not require refrigeration, they are more stable when stored under refrigeration. The stability of the capsule contents will be assessed at predetermined time points as described in Section 13.

### 6.2 Dosage, Preparation, and Administration of Study Drug

The dose of LGG for this study is  $1 \times 10^{10}$  LGG administered twice a day for 28 days. This dose has been widely used in studies of LGG described in Tables 1-3 above. When an order for study drug is received, the research pharmacist will retrieve the LGG capsules in the blister packs and place them in a plastic bag. The plastic bag is labeled with the following information:

- Subject study ID
- Name of subject
- Name of study/protocol number
- MD prescribing the study drug

- Directions
- Quantity dispensed
- Dispensing date
- “Study Drug”
- Expiration date
- Storage requirements “Keep at or below room temperature”

The study drug will be sent to the CRC where research study staff will dispense it to the subject, along with clear instructions on proper use of the study drug. An instruction sheet on taking the LGG will be given to all subjects and the first dose will be administered under direct observation in the CRC.

### **6.3 Accountability Procedures for the Study Drug**

The study pharmacist and/or study coordinator will keep source documentation for accountability of study drug that details receipt, dispensing, and return of used and unused study drug. Study drug will be inventoried and accounted for throughout the study. All study drugs will be stored in locked facilities until they are either returned to Amerifit Brands, Inc. at the closure of the study or at an earlier time point if requested, or destroyed by the pharmacy. Prior to dispensing, blister packs containing study drug will be visually inspected. If a blister pack appears to have tears or signs of tampering, the blister pack will be rejected for use and retained until the end of the study. At the end of the study, Amerifit Brands, Inc. will determine dispensation of all remaining unused blister packs at the study site. An accountability log will be kept, indicating the final disposition of study drug. This log will be provided to the Principal Investigator at the end of the study.

### **6.4 Assessment of Subject Compliance with Study Drug**

At the 28 day study visit, subjects will be asked to bring in all remaining study drug. Study staff will count and record the number of study drug capsules brought back.

### **6.5 Concomitant Therapy**

All medications taken within 30 days prior to the administration of study drug and all concomitant medications administered during the study are to be recorded on the relevant case report form page(s), along with the reason for use. All prior hospitalizations as well as all surgeries will be recorded on the relevant CRF page(s). Subjects using LGG or other probiotics (including yogurt displaying the “live and active cultures” seal) within 28 days will be excluded from participating in the study, unless they are willing to discontinue these products for 28 days before their baseline visit and for the duration of the study. Those who consume yogurt will be eligible only if they

consume yogurt brands sold in the United States that are heat-treated, thus have active cultures destroyed. During the study period, subjects will be asked to avoid consuming brands of yogurt that display the “live and active cultures” seal (as listed by the National Yogurt Association’s seal program – [www.aboutyogurt.com/lacYogurt](http://www.aboutyogurt.com/lacYogurt)).

## **7 STUDY SCHEDULE**

The schedule of evaluations and procedures that must be performed at specific time points is described in the following sections and is summarized in the Time and Event Schedule (page 11).

### **7.1 Screening (Visit Day -31 to Day -1)**

Potential subjects for this study will be scheduled for a screening visit. At the start of the visit, the nature of the study will be explained to him/her by the study investigator or designee, and the potential subject will be asked to give written informed consent and sign the HIPAA authorization. Informed consent/HIPAA authorization must be obtained prior to any procedures occurring. Subjects will be asked to describe their medical history (including a review of all inclusion and exclusion criteria), and have a physical examination (with vital signs) and laboratory tests. HIV testing will be performed according to the Tufts Medical Center's and Massachusetts General Hospital standard procedure, after the subject has signed the Tufts Medical Center or Massachusetts General Hospital standard HIV testing consent form. The specific procedures during the screening visit include:

- Demographics, medical history and review of inclusion and exclusion criteria, concomitant therapy/medications, consumption of probiotics, yogurt, etc.
- Physical exam with height, weight and vital signs
- Routine Laboratory tests
  - CBC
  - Serum chemistries/liver function tests
  - Drug and alcohol toxicity screen
  - Serology for anti-HIV, anti-HCV, and Hepatitis B surface antigen (HbsAg)

Subjects are provided with information on foods and probiotic products to avoid during the study, a stool sample collection kit and instructions on how to collect stool specimens should they be eligible to participate in the study.

### **7.2 Enrollment (Baseline Visit, Day 0)**

Subjects who are eligible to participate in the study after all of the screening tests have been completed will return for a baseline visit. The following evaluations and procedures will be done at the baseline visit, prior to receiving the study drug:

- Interval medical history, concomitant therapy/medications, consumption of probiotics, yogurt, etc and review of symptoms

- Physical exam with weight and vital signs
- Routine Laboratory tests
  - CBC
  - Serum chemistries/liver function tests
- Breathalyzer - Alcohol screen
- Research Laboratory tests
  - Collection of nasopharyngeal specimens for microbiota
  - Collection of stool sample for microbiota and LGG culture

Enrolled subjects will be offered an opportunity to participate in the sub-study. After they either decline or accept, study drug will be dispensed.

- Study drug cultures for colony counts
- First administration of study drug. Subject will learn how to take the study drug twice daily for the next 4 weeks.
- Sub-study only – blood for DNA, mRNA and cytokines

Subjects will be reminded to contact the PI at any time for any study related issues or adverse events that occur. Subjects will receive a new stool container and again be instructed on how to collect the stool.

